### (6) Piloting of the complex intervention (feasibility and piloting phase): Pilot study

**Aim:** The main objective of the pilot study is to estimate the effect size in order to plan the sample size for the main cluster-randomized trial. 

**Participants and design:** The pilot study will be designed as a cluster randomized controlled study to assess the feasibility of the developed intervention and its components. Target population for the pilot study will be residents with joint contractures in six nursing homes in the area of Munich, Halle and Witten. Presence of joint contractures will be evaluated by either physicians’ diagnosis or the diagnosis of a skilled staff nurse or physical therapist. There will be no other inclusion criteria. We will exclude residents with limited life expectancy due to advanced cancer or other diseases with poor prognosis according to the assessment by the nurse in charge. Each nursing home will be randomly assigned to the intervention group or to the control group. In line with suggestions of Billingham et al. [42] we will include a total sample size of about 120 residents, 60 in the intervention and 60 in the control group.

The primary outcome will be the impact of joint contractures on functioning and participation as measured by a recently developed instrument [27]. This outcome measure consists of a selection of categories of the International Classification of Functioning, Disability and Health (ICF), operationalized in a consensus meeting among clinical experts. This selection is currently being validated according to its psychometric properties with an emphasis on specific objectivity in the sense of Rasch analysis [43]. This Rasch-validated instrument will be used as primary outcome measure. Secondary outcomes will be collected using established instruments fitting the intervention components.

We also collect gender, age, socioeconomic variables, activities of daily living through Barthel Index [44], Mini Mental State Examination [45], and presence of chronic diseases [46] as potential confounders.

**Analysis:** The effects of the intervention over 6 months will be analysed on an intention-to-treat basis. Group differences will be assessed by mean and standard deviation. In addition, the influence of different nursing home characteristics (e.g. staffing characteristics, ward size etc.) will be assessed using multiple regression models. Also results of the process evaluation will be taken into account when interpreting the results of the pilot study. 

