## Abstract

**Background:** Joint contractures are common problems in frail older people in nursing homes. Irrespective of the exact extent of older individuals in geriatric care settings living with joint contractures, they appear to be a relevant problem. Also, the new emphasis on the syndrome of joint contractures, e. g. by the German statutory long term care insurance, led to an increase in assessment and documentation efforts and preventive interventions in clinical care. However, more attention should be paid to the actual situation of older individuals in nursing homes with prevalent joint contractures, particularly their experience of related activity limitations and participation restrictions. Thus, the aim of this study is 1) to develop a tailored intervention to improve functioning, and especially participation and quality of life in older residents with joint contractures in nursing homes and 2) to test the feasibility of the intervention accompanied by a rigorous process evaluation.

**Methods:** The complex intervention, which will be developed in this project follows the UK Medical Research Council (MRC) framework and integrates the perspectives of all potentially relevant user groups, from the affected individuals to clinicians and researchers. The development process will comprise a systematic literature review, reanalysis of existing data and the integration of the knowledge of the affected individuals and experts. The developed intervention including a comprehensive process evaluation will be pilot tested with residents with joint contractures in three nursing homes.

**Discussion:** The projected study will provide a tailored intervention to improve functioning, participation and quality of life in older residents with joint contractures in nursing homes. With this focus, the intervention will support patient relevant outcomes. The pilot study including process evaluation will offer a first opportunity to indicate the size of the intervention’s effect and prepare further studies.

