As proofs of effectiveness are missing for the primary and secondary preventive interventions that are part of the current standard of care in joint contractures, an alternative focus should be on interventions which do not merely address prevention or treatment of joint contractures but also focus on maintaining or enhancing participation and quality of life. Thus, more attention should be paid to the actual situation of older individuals in nursing homes with prevalent joint contractures, particularly their experience of related activity limitations and participation restrictions. To address this issue, we have recently developed a standard set based on the WHO’s International Classification of Functioning, Disability and Health (ICF) [18] to comprehensively describe activity limitations and participation restrictions and are developing a standardized assessment instrument to quantify the extent of activity limitations and participation restrictions [19]. Based on the results of the preceding project the next step is now to develop an intervention to address the actual situation of older individuals in nursing homes with prevalent joint contractures. Hence, the aim of this study is 1) to develop a tailored complex intervention to improve functioning, and especially participation and quality of life in older residents with joint contractures in nursing homes and 2) to test the feasibility of the intervention and the process evaluation tools in a pilot study. 

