## Methods

The development of relevant, effective and feasible health care interventions is challenging, since changes in health care practice are rather complex than deterministic. To address these issues und to ensure the development of theoretically and empirically plausible, consumer-orientated and feasible interventions, the UK MRC framework was introduced to provide guidance on how to develop and evaluate complex interventions. It identifies the following four key elements of this potentially cyclical process: development, feasibility/piloting, implementation and evaluation. This study protocol focuses on the development and the feasibility/piloting phases. The development phase usually includes identification of the relevant evidence base, identification or development of a theory and modelling of the intervention process and the addressed outcomes. In the feasibility and piloting stage, the acceptability and feasibility of the developed intervention is carefully assessed. Also, recruitment procedures and recruitment and retention rates have to be evaluated. In addition, the basis for sample size calculations can be investigated in this phase [20], [21]. Based on this framework, our study has a design with seven successive steps. 

An overview of all applied methods and designs is given in Table 1 (Tab. 1). 

The study protocols of all empirical parts of the projects will be presented to the respective ethics committees of the Ludwig-Maximilians-Universität in Munich and the Martin-Luther-University in Halle-Wittenberg prior to the start of the respective part. Written informed consent from the participants or their legal guardians will be obtained prior to inclusion in the study.

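### The pilot's main objective is an effect size for planning the main trial, but six randomised homes with about 120 residents cannot estimate it precisely enough for that use

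*Protocol article*

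**What the plan says.** The Aim of step (6) in the protocol article reads: "The main objective of the pilot study is to estimate the effect size in order to plan the sample size" of the main cluster-randomized trial. The next paragraph adds feasibility: "The pilot study will be designed as a cluster randomized controlled study to assess the feasibility of the developed intervention and its components". The setting is "residents with joint contractures in six nursing homes in the area of Munich, Halle and Witten", and "Each nursing home will be randomly assigned to the intervention group or to the control group". On size, "we will include a total sample size of about 120 residents, 60 in the intervention and 60 in the control group"; the only support given is a cited suggestion on pilot sample sizes.

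The Analysis paragraph of step (6) describes the group comparison over 6 months by mean and standard deviation. The Abstract expects the pilot to give a first indication of how large the effect is. The article states no ICC, SD, target precision or minimal important difference.

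**The concern.** The plan names one main output, an effect size, and one use for it, sizing the next trial. The sample is counted in residents, 60 per arm, whereas whole homes are randomised. Information about the treatment contrast is limited by the number of homes: six homes in two arms leave 4 between-home degrees of freedom, and no later analysis can add to that.

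If the estimate is high by chance, a main trial planned on it is too small. If it is low by chance, the main trial is far larger than needed or looks impossible to run. The Discussion says the project is meant to reduce failures of this kind through careful development.

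**Working it through.** **The plan's own figure.** 60 + 60 = 120 agrees. The article gives no calculation behind it, so nothing more can be reproduced.

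**Inputs from the protocol article, step (6).** Six homes, randomised whole; 60 residents per arm.

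**Assumptions, because the article gives none.** Three homes per arm, 120/6 = 20 residents in each, SD 1 (effects in SD units), no dropout, ICC 0 to 0.10, true effect d of 0.2 to 0.5. For the main trial: two-sided 5% level, 80% power, same cluster size.

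**Step 1: precision of the pilot estimate.** Design effect DE = 1 + (20 − 1) × ICC. SE = √((2/60) × DE). The 95% half-width is t(0.975; 4 df) × SE = 2.776 × SE.

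| ICC | DE | SE | 95% half-width, 4 df |
|---|---|---|---|
| 0 | 1.00 | 0.18 | 0.51 |
| 0.02 | 1.38 | 0.21 | 0.60 |
| 0.05 | 1.95 | 0.25 | 0.71 |
| 0.10 | 2.90 | 0.31 | 0.86 |

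The most favourable case is no clustering with a normal quantile: 1.96 × 0.183 = 0.36 SD. At ICC 0.05, an observed effect of 0.3 would carry an interval of 0.3 ± 0.71, that is −0.41 to 1.01.

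**Step 2: how far the point estimate can stray.** At ICC 0.05 (SE 0.255), with a normal sampling distribution, P(estimate ≤ 0) = Φ(−d/SE) and P(estimate > 1.5d) = 1 − Φ(0.5d/SE).

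**Step 3: consequence for the main trial.** Size per arm from an estimate e is 2 × (1.96 + 0.842)² / e² × DE. With the ICC treated as known, DE cancels and true power is Φ(2.80 × d/e − 1.96). Power falls below 50% when e exceeds (2.80/1.96) × d = 1.43d. The share of trials below 50%, among pilots with a positive estimate, is P(e > 1.43d) / P(e > 0):
- d = 0.2: 0.368/0.784 = 47%
- d = 0.3: 0.307/0.880 = 35%
- d = 0.5: 0.200/0.975 = 20%

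Mean true power is the average of the power formula over simulated positive estimates.

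| At ICC 0.05, true d | 0.2 | 0.3 | 0.5 |
|---|---|---|---|
| P(estimate ≤ 0) | 22% | 12% | 2.5% |
| P(estimate > 1.5d) | 35% | 28% | 16% |
| Mean true power, given a positive estimate | 59% | 67% | 74% |
| True power below 50%, given a positive estimate | 47% | 35% | 20% |

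**Step 4: the middle half of outcomes.** At d = 0.3 and ICC 0.05, about 341 residents per arm are needed. The quartiles of the pilot estimate are 0.3 ± 0.674 × 0.255 = 0.13 and 0.47. They lead to about 1,864 and 138 per arm, the latter with true power of about 43%. With ICC 0 and the same effect, the quartiles give 502 and 88 per arm against 175 needed, with power of about 51% at the upper quartile.

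The 4-df widening applies to the interval in step 1. Steps 2 to 4 use normal draws and a known ICC, so they are a separate and somewhat kinder model.

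**The case against.** The pilot literature that the article follows does give sample size planning as a function of this phase: Methods says the basis for sample size calculations can be investigated here. The Abstract is modest, promising only a first indication of the effect. The Analysis paragraph says process-evaluation results will inform interpretation, and nothing states that the point estimate alone will set the main trial's size. The damage would occur only at the next planning stage, where it could still be avoided. The power figures also depend on the assumed effect and are milder at 0.5 SD than at 0.2 SD.

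Much of this is fair and limits the point, but it does not remove it. A basis for sample size calculations can mean the SD, attrition and cluster sizes; it does not require the treatment effect. The Aim nevertheless names the effect and its use.

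Three stronger readings are tempting and not supported:
- **That the plan contradicts itself.** Background gives the aim as "to test the feasibility of the intervention and the process evaluation tools in a pilot study", but that covers the whole project, and step (6) pairs the effect objective with feasibility in the same section. This is a difference of emphasis.
- **That retention has been forgotten.** The sentence "Also, recruitment procedures and recruitment and retention rates have to be evaluated" describes the general framework, and the list under step (7) is condensed, as journal articles are.
- **That a good intervention would be stopped, or a lucky one selected, by a go/no-go threshold.** The article contains no such threshold.

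**Conclusion.** The point holds on precision alone. The stated main objective needs an effect estimate fit for planning. The stated design gives one with a 95% half-width of 0.51 to 0.86 SD over ICC 0 to 0.10, and 0.36 SD at the very best. A main trial planned on it is likely to be badly under- or over-sized. A reader might infer that it is certain to be mis-sized; that goes too far, since this is a matter of probability.

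The direction does not depend on one assumed value: it holds for every ICC from 0 to 0.10 and every effect from 0.2 to 0.5 SD examined. The exact percentages do depend on the assumptions of equal homes of 20, no dropout and a known ICC.

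The calculation uses the six homes of step (6). The Abstract says the intervention "will be pilot tested with residents with joint contractures in three nursing homes". If only three homes took part in all, 3 − 2 = 1 between-home degree of freedom would remain. That discrepancy is a separate matter to reconcile.

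**What to change.** In step (6), reword the main objective as feasibility (recruitment, retention over 6 months, fidelity, completeness of the primary outcome) and outcome variability (pooled SD, cluster-size variation).

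State that the main trial's target difference will be a prespecified minimal important difference on the primary instrument, set once its validation is complete, and not the pilot point estimate. The experts already being consulted in steps (4) and (5) could contribute.

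Take the main trial's ICC from external data combined with the pilot, allowing for its uncertainty. The pilot alone will not do: in simulation with six homes of 20 and a true ICC of 0.05, 95% of the estimates fell between about −0.04 and 0.20.

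Report the pilot effect as exploratory, with a cluster-adjusted 95% confidence interval. Do not write an effective sample size into the protocol, since it would rest on assumed ICCs.

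**Cost.** The pilot gives up the claim to deliver the planning effect. Setting a minimal important difference on an instrument still under validation takes real work, more than one added question. No extra residents or homes are needed.

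### Multiple regression on several nursing home characteristics is planned with only six homes, which can support description but not the estimation of separate influences

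*Protocol article*

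**What the plan says.** All of this is in the protocol article, step (6) Pilot study, unless noted.

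- The setting is "six nursing homes in the area of Munich, Halle and Witten", and "Each nursing home will be randomly assigned to the intervention group or to the control group". Arm is therefore itself a home-level variable.
- The planned size is "a total sample size of about 120 residents, 60 in the intervention and 60 in the control group".
- The main comparison is descriptive: "Group differences will be assessed by mean and standard deviation".
- As an addition to that comparison, "the influence of different nursing home characteristics (e.g. staffing characteristics, ward size etc.) will be assessed using multiple regression models".

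The article names two characteristics and leaves the list open. It sets no limit on how many enter a model, does not call the analysis exploratory, and does not mention clustering or the small number of homes. It gives no ICC and no significance level.

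The Abstract gives a different number of homes: the intervention will be "pilot tested with residents with joint contractures in three nursing homes". The two statements need to be reconciled. The working below uses six, the figure in the Methods.

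**The concern.** The regression is meant to say which features of a home influence the result. Staffing and similar features vary between homes, so the number of independent observations for them is the number of homes. With six homes and one degree of freedom already taken by arm, a model with two or more characteristics has almost nothing left from which to judge error.

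At stake is how the output is read. Coefficients that mainly reflect chance differences among six homes would be reported as influences. They would come from a pilot whose purpose is to prepare a larger cluster trial.

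**Working it through.** **Inputs.** From step (6): 6 homes, 60 + 60 = 120 residents, home as the unit of randomisation, two named characteristics plus an open list. Assumed: equal homes (120 / 6 = 20 residents each), three homes per arm, and ICC values from 0 to 0.10, because the article gives none. The sample size rests on a cited source with no power calculation, so there is no further figure to reproduce.

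**Step 1: between-home degrees of freedom.** With k home characteristics beside arm, residual df = 6 − 1 (intercept) − 1 (arm) − k = 4 − k.

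**Step 2: variation explained by chance.** If neither arm nor the characteristics have any effect, arm plus k characteristics explain on average (1 + k)/5 of the variation between home means.

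| k | Residual df | Critical t (two-sided 5%) | Mean share explained by chance |
|---|---|---|---|
| 1 | 3 | 3.18 | 2/5 = 40% |
| 2 | 2 | 4.30 | 3/5 = 60% |
| 3 | 1 | 12.71 | 4/5 = 80% |
| 4 | 0 | none | 5/5 = 100% |

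With the Abstract's three homes, residual df = 3 − 2 − k, so a single characteristic already leaves 0.

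**Step 3: if clustering is respected.** In a null simulation, regression on the six home means kept the false-positive rate at about 5% per coefficient for k = 1, 2 or 3. The error rate is right, but at k = 2 an estimate must exceed 4.30 standard errors to stand out.

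**Step 4: if residents are treated as independent.** Set the total variance to 1.

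- The true variance of a home-level coefficient exceeds its independent-residents value by the design effect 1 + 19 × ICC.
- The residual variance that the model estimates is on average [114 × (1 − ICC) + (4 − k)(1 + 19 × ICC)] / (118 − k).
- At ICC 0.05 and k = 2 the design effect is 1.95 and the residual variance is (114 × 0.95 + 2 × 1.95)/116 = 112.2/116 = 0.967.
- The test statistic is too large by √(1.95/0.967) = 1.42. The nominal cut-off of 1.98 then acts like 1.98/1.42 = 1.39, with a two-sided normal tail of about 16%.

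A null simulation with 200,000 runs per setting agrees to within about one percentage point:

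| Assumed ICC | Per coefficient, k = 1 | k = 2 | k = 3 | At least one of two false |
|---|---|---|---|---|
| 0 | 5% | 5% | 5% | 9% |
| 0.02 | 10% | 10% | 10% | 17% |
| 0.05 | 17% | 17% | 17% | 28% |
| 0.10 | 26% | 26% | 27% | 42% |

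The per-coefficient rate hardly moves with k. The inflation comes from ignoring clustering, not from the number of characteristics. The last column also contains ordinary multiplicity, so its reference value is 9%, not 5%.

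**The case against.** The best defence is that the article names no unit of analysis, no significance test and no clustering method. A condensed article may leave all three to a fuller document. The list of characteristics gives examples, and the word models is plural, so one characteristic per model fits the text and leaves 3 df. If staffing or ward size were recorded by ward, there would be some variation within homes. The analysis is an addition in a pilot, and step (7) already plans a descriptive and qualitative study of context.

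Much of this stands. Resident-level regression is one possible reading, so the inflated rates are conditional on it and on an ICC above zero. The degree of near-saturation depends on how many characteristics enter together.

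Two stronger readings are tempting and are not supported:

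- A reader might infer that near-saturation by itself produces false significant findings. The tables show otherwise: with between-home df the result is imprecise, not falsely positive.
- A reader might infer that the characteristics confound the arm effect and so spoil the effect size that the pilot is to deliver. The article assesses group differences separately, by mean and standard deviation, and does not say that the effect size comes from this regression.

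The defence does not remove the core. The article calls these nursing home characteristics and plans multiple regression on more than one. An analysis plan could correct the error rate, but it cannot add homes.

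**Conclusion.** The point holds as a badly chosen secondary analysis. With six homes, arm plus the two named characteristics leave 2 between-home df, and irrelevant characteristics would on average seem to account, together with arm, for 60% of between-home variation. If clustering is respected, the analysis says almost nothing. If residents are treated as independent, it gives too many false influences: about 10%, 17% and 26% per coefficient at ICCs of 0.02, 0.05 and 0.10.

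The df count rests on the article's six homes and on one value per home for each characteristic. The false-positive rates also rest on assumed ICCs, equal homes of 20 and an unadjusted resident-level model that the article does not specify. The pilot's main descriptive comparison of the arms is not affected. The change is worth making because it is cheap and prevents results that cannot be interpreted.

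**What to change.** Replace the multi-characteristic regression with a descriptive table or plot of the six homes, showing for each home its arm, number of residents, staffing, ward size and mean change in the primary outcome. Interpret it alongside the process evaluation in step (7).

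If a model is kept, allow at most one home-level covariate beside arm per model, account for clustering, use between-home degrees of freedom (3 with six homes) and label the result exploratory. State that inference on home characteristics is left to the main trial. Reconcile the number of homes between the Abstract and step (6).

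The cost is a change of wording. What is lost is a set of multi-covariate coefficients that six homes cannot support.

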### (7) Piloting of the complex intervention (feasibility and piloting phase): Process evaluation 

**Aims:** To evaluate the context of the trial and to learn from the factors which are associated with successful or failing implementation of the intervention components, a process evaluation will be carried out alongside the pilot study. Also, it is intended to use the process evaluation of the pilot study to prepare the process evaluation of the subsequent main trial. 

**Participants and design:** This process evaluation will follow the framework provided by Grant et al. [47] and will address recruitment, reach and fidelity of the intervention, satisfaction of users, staff and organizations. Also, the data collection procedures of this pilot study will be used to test instruments and methods required for recording the cost data relevant for an economic evaluation alongside the main trial. The process evaluation will use quantitative and qualitative methods (numeric evaluation of recruitment and reach via checklists and scales, individual interviews with residents and focus groups for the nursing and therapeutic staff and the management of the nursing homes). The aim to minimize bias in the process evaluation will be reached by implementing different aspects of data collection with the use of standardized instruments, focus group interviews, quantitative and qualitative methods. 

**Analysis:** Results of the process evaluation will be analysed with descriptive statistics and qualitative descriptive methodology [36], [39].

To improve overall scientific quality, an external advisory board with clinicians and methodological experts will be established.

